### Study outcomes

The *primary efficacy outcome* of the study will be an objectively documented symptomatic recurrence or extension of SVT, symptomatic DVT (proximal or distal), asymptomatic proximal DVT, symptomatic pulmonary embolism (fatal / nonfatal), or death, whichever comes first, during the treatment period.

The *secondary efficacy outcome* will be: the occurrence of asymptomatic recurrence, extension, or asymptomatic distal DVT; the rVCSS score and the VEINES / Sym-QoL questionnaire; the impact of elastic compression therapy on SVT treatment; the association between CRP levels and primary efficacy outcomes; the natural history of SVT in patients allocated to placebo; the evaluation of the prolonged protective effect of mesoglycan after the first 12 months of treatment.

The *safety outcome* will be the incidence of major bleeding, as defined by the International Society on Thrombosis and Hemostasis (ISTH) criteria: fatal and/or symptomatic bleeding in a critical area or organ (e.g., intracranial, intraspinal, intraocular, retroperitoneal, intraarticular, pericardial, intramuscular with the associated compartmental syndrome); and/or in the case of clinically overt bleeding associated with a hemoglobin decrease of at least 20 g/L or requiring transfusion of 2 or more units of packed red blood cells [40].

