### Final analysis of the primary endpoints

The primary cumulative efficacy endpoint will be the occurrence of the first event among the event types considered. The hypothesis of superiority of the primary cumulative efficacy endpoint will be tested by multivariate Cox proportional hazards regression using as covariates the assigned drug, age at randomization, sex, compliance with treatment, and the additional risk factors for DVT and DVT/PE found to be significantly associated in the univariate analysis (between obesity, varicose veins, cancer, standing or prolonged immobilization, recent surgery, severe infections, prior DVT/PE, thrombophilia, chronic heart failure NYHA III-IV, use of estrogen-progestogens). All variables participating in the model will be tested for the assumption of proportionality of the risks with the usual graphical method. In addition, a significant subset of variables will be chosen with the Wald method and in a “forward stepwise.”

The crude and adjusted cumulative proportion of event-free subjects over follow-up in the two treatment groups will be described with Kaplan–Meier plots.

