### Final analysis of secondary endpoints

For the analysis of the secondary efficacy endpoints, the following will be used:the Kaplan–Meier plot of the cumulative occurrence over time and the log-rank test to compare the two treatment arms,for the rVCSS scores, analysis of variance for repeated measures will be used (all available assessments for within-subject effects and the 2 treatment groups as between-subjects effect).in the case of the VEINES/Sym-Qol scores, the analysis of variance for repeated measures will be used (all evaluations available for the within-subject effect and the 2 treatment groups as the between-subjects effect).The impact of elastic compression therapy in the various endpoints will be analyzed by inserting it as a stratification factor in the related analyzes.The predictive contribution of CRP levels (subdivided by tertiles) to the primary efficacy endpoint will be analyzed by insertion as a stratification factor in relative analyzes.

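### Used as a stratification factor in the time-to-event analyses, CRP is adjusted away rather than estimated, so the stated method does not fit the CRP objective; the case for elastic compression is weaker

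*Protocol article*

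**What the plan says.** The protocol article's section Study outcomes lists among the secondary efficacy outcomes "the impact of elastic compression therapy on SVT treatment; the association between CRP levels and primary efficacy outcomes".

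The section Final analysis of secondary endpoints gives the method for each. For CRP: "The predictive contribution of CRP levels (subdivided by tertiles) to the primary efficacy endpoint will be analyzed by insertion as a stratification factor". For compression: "The impact of elastic compression therapy in the various endpoints will be analyzed by inserting it as a stratification factor in the related analyzes".

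The time-to-event analyses into which these factors would go are:
- for the primary endpoint, "multivariate Cox proportional hazards regression using as covariates the assigned drug, age at randomization, sex, compliance with treatment", plus risk factors selected by univariate analysis from the list "between obesity, varicose veins, cancer, standing or prolonged immobilization, recent surgery, severe infections, prior DVT/PE, thrombophilia, chronic heart failure NYHA III-IV, use of estrogen-progestogens";
- for secondary event endpoints, Kaplan–Meier plots and "the log-rank test to compare the two treatment arms".

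Neither CRP nor compression is among the fixed covariates or the candidate risk factors. No interaction term is stated for either.

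**The concern.** An objective about association or predictive contribution needs an estimate of how the event rate changes with the variable, and a test or interval for it. In survival analysis, a stratification factor has an established meaning that works against this: the variable is allowed any effect on the baseline hazard so that it can be removed from the comparison of interest, here mesoglycan against placebo.

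An analyst who followed the text in that sense would report the treatment hazard ratio again, adjusted for CRP, and have nothing to report about CRP itself. The decision between a stratum and a covariate or grouping factor would then still have to be made, and it determines whether the secondary outcome has an inferential result.

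**Working it through.** **Step 1: what stratification does to the variable.** Suppose the true hazard for patient *i* in CRP tertile *s* is h₀(t)·exp(βxᵢ + γₛ), where x is treatment and γₛ is the CRP effect. In the stratified Cox model, risk sets are formed within tertile, so each event contributes

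exp(βxᵢ + γₛ) / Σⱼ exp(βxⱼ + γₛ) = exp(βxᵢ) / Σⱼ exp(βxⱼ), with the sum over patients *j* at risk in the same tertile.

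γₛ cancels, and β is the only parameter left. The stratified log-rank statistic behaves in the same way: (Σₛ(Oₛ − Eₛ))² / Σₛ Vₛ compares treatment arms within each tertile and never compares tertiles.

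**Step 2: simulation at the planned size.** The documents give no figure for the CRP effect, so there is none to reproduce.

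Inputs from the section Statistical analysis and sample size: 650 patients at 1:1, 12-month placebo risk 15%, HR 0.5, 10% loss. Assumptions: exponential event and loss times, 12 months at risk, three equal tertiles, and a CRP effect of either HR 1.0 or HR 1.6 per tertile (top versus bottom 1.6² = 2.56). There were 150 simulated trials per scenario.

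| Analysis | CRP HR 1.0 per tertile | CRP HR 1.6 per tertile |
|---|---|---|
| Cox stratified by tertile: treatment HR | 0.497 | 0.487 |
| Cox stratified by tertile: CRP estimate | none | none |
| Cox with tertile as covariate: treatment HR | 0.497 | 0.487 |
| Cox with tertile as covariate: top vs bottom HR | 1.07 (true 1.00) | 2.67 (true 2.56) |
| Log-rank between tertiles, stratified by arm: rejection at 5% | 6.7% | 81% |

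The 6.7% is compatible with 5% in 150 runs, where the standard error is √(0.05 × 0.95 / 150) = 1.8 percentage points. The stratified model gives almost the same output whether CRP matters or not. The covariate model and the between-tertile log-rank test both separate the two cases. The treatment HR is the same to three decimals with tertile as a stratum or as a covariate.

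**Step 3: can the model carry the extra term?** Write f(λ) = λ/(λ+δ)·(1 − e^−(λ+δ)), with λ = −ln 0.85 = 0.1625 for placebo, half of that for mesoglycan, and δ = −ln 0.90 = 0.1054. Then f = 0.1426 and 0.0741, which sum to 0.2167.
- With 325 per arm: 325 × 0.2167 = 70 events.
- With the 570 patients the abstract reports as randomised: 285 × 0.2167 = 62 events.

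One degree of freedom for log-CRP, or two for tertiles, is affordable.

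**Step 4: where compression differs.** CRP is tied only to the primary, time-to-event endpoint. Compression is to be examined across several endpoints, including the rVCSS and VEINES/Sym-QoL scores. These are analysed by repeated-measures ANOVA, where an added between-subjects factor is estimated and tested. The gap for compression is therefore confined to the event endpoints.

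**The case against.** The strongest reply is that the protocol uses the word loosely. The section never refers to a stratified Cox model or to separate baseline hazards. The section Treatment compliance calls compliance a possible stratification variable, while Final analysis of the primary endpoints enters it as a covariate. Forming tertiles to study a predictive contribution also fits a grouping factor whose levels are compared. Under that meaning the CRP question has an answer, as the 81% rejection rate shows. Kaplan–Meier curves by tertile would at least describe any difference. How a factor enters each model is also the kind of detail an analysis plan, not shown here, may settle.

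Much of this stands. A reader might infer that the two questions cannot be answered at all; the documents do not support that. For compression the inference fails further. The ANOVAs would estimate its effect, and the stated outcome, its impact on SVT treatment, may mean effect modification. Treatment effects within compression groups address that in part, although no interaction test is stated. Nor is the use of tertiles in place of continuous CRP an error; it is a design choice with some loss of information.

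The reply does not remove the point. The method is stated, not merely left out, and its ordinary meaning in the named analyses does not serve the stated objective. The log-rank test is specified to compare treatment arms, so using tertile as its grouping factor departs from the text. The two meanings lead to different results, one with a CRP estimate or test and one without.

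**Conclusion.** The point holds in a limited form. Read literally for the time-to-event endpoints, stratifying by CRP tertile neither estimates nor tests the CRP effect, so the method does not fit the secondary outcome it is meant to serve. This is clear for CRP. It is weaker for compression and applies there only to the event endpoints.

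The algebra rests on the standard meaning of a stratified Cox model or log-rank test. The numerical illustration also rests on an assumed CRP effect of HR 1.6 per tertile and the protocol's planning figures. If the trial team means a covariate or grouping factor, the correction is one of wording. The primary treatment comparison, sample size, alpha and safety analysis are not affected.

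**What to change.** In Final analysis of secondary endpoints, replace the stratification wording as follows.

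- **CRP:** in a secondary Cox model for the primary endpoint, baseline CRP enters as a covariate alongside treatment, age and sex, either as continuous log-CRP or in the tertiles now planned. Report its HR with confidence interval, and show Kaplan–Meier curves by tertile.
- **Elastic compression:** it enters the Cox models as a covariate. If the question is whether compression alters the effect of mesoglycan, add and report a treatment-by-compression interaction. In either case label the comparison as non-randomised.

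The cost is wording and one or two extra model degrees of freedom. CRP is already in the blood sample taken at inclusion (Study population and randomization), so no data collection is added for it. Because these are secondary models, the primary treatment comparison stays as planned.

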### Final analysis of the security endpoints

Analysis of the primary safety endpoint will be performed with the continuity adjusted chi-square test.

Standard summary of safety data related to adverse events and significant changes in laboratory data will also be provided.

## Data Availability

The data that support the findings of this study are not openly available due to reasons of sensitivity and are available from the corresponding author upon reasonable request.
